# Warwick Hip Trauma Study: a randomised clinical trial comparing interventions to improve outcomes in internally fixed intracapsular fractures of the proximal femur. Protocol for The WHiT Study

**DOI:** 10.1186/1471-2474-11-184

**Published:** 2010-08-17

## Abstract

**Background:**

Controversy exists regarding the optimal treatment for patients with displaced intracapsular fractures of the proximal femur. The recognised treatment alternatives are arthroplasty and internal fixation. The principal criticism of internal fixation is the high rate of non-union; up to 30% of patients will have a failure of the fixation leading to revision surgery. We believe that improved fracture healing may lead to a decreased rate of failure of fixation. We therefore propose to investigate strategies to both accelerate fracture healing and improve fixation that may significantly improve outcomes after internal fixation of intracapsular femoral fractures. We aim to test the clinical effectiveness of the osteoinductive agent platelet rich plasma and conduct a pilot study of a novel fixed-angle fixation system.

**Design:**

We have planned a three arm, single centre, standard-of-care controlled, double blinded, pragmatic, randomised clinical trial. The trial will include a standard two-way comparison between platelet-rich plasma and standard-of-care fixation versus standard-of-care fixation alone. In addition there will be a subsidiary pilot arm testing a fixed-angle screw and plate fixation system.

**Trial Registration:**

Current Controlled Trials ISRCTN49197425

## Background

### Epidemiology

Proximal femoral fractures are one of the greatest challenges facing the medical community. In 1990, a global incidence of 1.31 million was reported and was associated with 740,000 deaths [1]. Proximal femoral fractures constitute a heavy socioeconomic burden worldwide. The cost of this clinical problem is estimated at 1.75 million disability adjusted life years lost, 1.4% of the total healthcare burden in established market economies [1].

### Existing knowledge

Proximal femoral fractures can be subdivided into intra and extracapsular fractures. Approximately half of all proximal femoral fractures are intracapsular. These fractures are at risk of healing complications as the blood supply to the femoral head may be compromised by the fracture. There are two operative strategies in the management of intracapsular fractures of the proximal femur: internal fixation and hip arthroplasty.

Arthroplasty surgery eliminates the risk of fixation failure as the femoral head is replaced. However, it is a major operation with very significant complications of its own including infection, dislocation and periprosthetic fracture. The most common form of arthroplasty in this group of patients is hemiarthroplasty, where the head of the femur is replaced but the acetabulum is left intact, but this procedure is associated with an approximately 20% risk of late acetabular wear leading to arthritic changes and the potential need for further surgery [2]. Internal fixation has the key advantage of preserving the patients' own bone and cartilage. It is also a quicker operation requiring a much smaller wound. The principal complication of internal fixation is non-union which is related to the tenuous blood supply to the femoral head. However, the rate of non-union and fixation failure has been reported at up to 33%, [3] leading to re-operation in 90% of these patients. Consequently, the best treatment of these fractures remains controversial. A recent Cochrane review [4] has confirmed that the evidence suggests that there is no clinical benefit of one treatment over the other.

In order for any fracture to heal successfully there must be both a good biological environment and adequate fracture fixation. When a fracture heals there is a balance between the time required to achieve union and the time over which the fixation maintains fracture position. Therefore, the failure of a fracture to heal may be due to an inadequate biological environment (leading to a long healing time) or an inadequate fixation system (leading to a short period of effective fixation). Interventions to improve fracture healing are targeted at one of these two broad areas. In patients with intracapsular fractures of the proximal femur interventions to improve fracture healing may reduce the rate of fixation failure and therefore the requirement for major arthroplasty surgery.

### Aim of the trial

The aim of this trial is to investigate the clinical effectiveness of novel surgical interventions to improve clinical outcomes following fracture of the proximal femur. Currently, there are two new techniques available which have shown promising early results for the treatment of acute fractures: firstly, platelet-rich plasma (PRP) which is an autologous source of growth factors derived from a patient's whole blood; secondly, novel fixed-angle screw and plate systems which are available following developments in the field of fragility fracture fixation. Early results of both these interventions are promising but there is no Level I clinical data [5,6].

### Hypothesis

We propose to test the hypotheses that: PRP leads to a reduced incidence of failure of fixation in patients with intracapsular fractures of the proximal femur.

We propose to explore the size of any treatment effect due to a novel fixed-angle screw and plate system in the treatment of patients with intracapsular fractures of the proximal femur.

### The need for a trial

A review [4] from The Cochrane Database for Systematic Reviews 2007 states:

"Fractures of the thigh bone (femur) near the hip joint (termed intracapsular) may be treated by fixing the fracture (with screws or pins), or alternatively replacing the top of the femur at the hip joint (femoral head) with an artificial hip joint (arthroplasty). This review found that each treatment has its own specific complications. Realigning the bones and fixing the fracture (reduction and internal fixation) is a shorter operation with less blood loss, but is more likely to need a second operation (36% versus 11%). The reason for this is mainly from a failure of the bone to heal in those cases treated with fixation. Internal fixation is associated with less initial operative trauma but has an increased risk of re-operation on the hip."

A search of the national and international clinical trials databases has revealed that there is only one other trial that is being carried out in the USA [7]. This is a commercial trial assessing the use of bone morphogenetic protein (BMP) only. A commercial trial in Leeds, UK investigating the effect of BMP in proximal femoral fractures has recently been abandoned. Otherwise there is no high quality clinical research in this field.

### Good Clinical Practice

The trial will be carried out in accordance with Good Clinical Practice (GCP) and in accordance with the following protocol.

### CONSORT recommendations

The trial will be reported in line with the CONSORT statement [8].

## Methods

### Trial Design

#### Design summary

This trial will be a three arm single centre, standard-of-care controlled, double blinded, pragmatic, randomised clinical trial.

The study will include a standard two-way comparison between PRP and standard-of-care fixation versus standard-of-care fixation alone. This comparison will be the only hypothesis-testing analysis. In addition there will be a subsidiary pilot arm testing fixed-angle screw and plate fixation. This comparison will be a hypothesis-generating analysis only.

The trial is expected to last a total of two years. It is expected that participant recruitment will take one year and final follow-up will be at one year.

The trial was given ethical approval by the Coventry Research Ethics Committee on 6 May 2009.

#### Objectives of the trial

The objectives of this trial are to:

1. test the hypothesis that PRP leads to a reduced incidence of failure of fixation.

2. explore the size of any treatment effect of a novel fixed-angle screw and plate fixation system

#### Measures of efficacy

##### Primary

• The proportion of participants undergoing re-operation for failure of fixation within one year of sustaining the fracture.

##### Secondary

• Radiographic non-union rate at 12 months. Non-union will be defined as "failure of the fracture to show signs of bony union on the anteroposterior or lateral radiograph 1 year after surgery" [9].

• Radiographic evidence of failure of fixation at 6, 12 and 52 weeks

• Radiographic evidence of avascular necrosis at one year

• Magnetic resonance imaging at 6, 12 and 52 weeks. This measure will only be recorded for those participants with capacity.

• The EQ-5D score at 6, 12 and 52 weeks

• Length of index hospital stay

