### Statistical analysis plan

#### Analysis of efficacy

##### PRP vs standard-of-care (parallel cannulated screws)

The primary outcome measure, the proportion of patients requiring re-operation for failure of fixation within one year of sustaining the fracture, will be analysed using a chi-squared test for differences between internal fixation alone (control) and internal fixation and PRP (PRP) on an intention-to-treat basis. Treatments will be considered to differ significantly if p-values are <0.05 (5% level). Similarly, chi-squared tests will be used to assess the significance of observed differences for the secondary proportional outcome measures. If the numbers in the contingency tables are small (cells with values below 10) then Fisher's exact test will be used in preference to the chi-squared test. In addition to the main analysis, that will report treatment group effects for the primary outcome measure, a subsidiary analysis will use a multiple linear regression model to investigate the relationship between each patient's EQ-5D Score at 12 months and the treatment arm, age, gender, dementia and fracture displacement for each patient. Estimates, and 95% confidence intervals, from the regression model, and unadjusted results from t-tests will be reported and inferences made on the significance of the treatment effect. All analyses will be based upon an intention-to-treat analysis so missing data due to protocol violations will not be relevant. The primary outcome measure in this study has been chosen in order to limit the possibility of losing data from failed participant follow-up. The primary measure can be sourced from the patient, relative, GP or national hp fracture database.

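### Non-union is defined only by the 1-year film, which cannot classify hips converted to arthroplasty, so the secondary comparison loses most of its events and is hard to interpret

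*Protocol article*

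**What the plan says.** All references are to the protocol article.

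- **Measures of efficacy, Secondary.** Non-union is "failure of the fracture to show signs of bony union on the anteroposterior or lateral radiograph 1 year after surgery". Avascular necrosis is "Radiographic evidence of avascular necrosis at one year"; Table 3 lists it at week 52 only. A third radiographic outcome has several time points: "Radiographic evidence of failure of fixation at 6, 12 and 52 weeks".
- **Measures of efficacy, Primary.** "The proportion of participants undergoing re-operation for failure of fixation within one year of sustaining the fracture".
- **Background, Existing knowledge.** "the rate of non-union and fixation failure has been reported at up to 33%, [3] leading to re-operation in 90% of these patients". Better healing "may reduce the rate of fixation failure and therefore the requirement for major arthroplasty surgery". The same section notes that arthroplasty replaces the femoral head.
- **Statistical analysis plan, PRP vs standard-of-care.** "chi-squared tests will be used to assess the significance of observed differences for the secondary proportional outcome measures", with Fisher's exact test where cells fall below 10. Missing data are discussed only in relation to protocol violations, which intention-to-treat is said to make irrelevant.
- **Data management.** Table 3 records re-operation, and radiographic union and fixation, at weeks 6, 12 and 52. Gaps are to be filled from clinical databases and case report forms.

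The article does not say how a hip re-operated before the 1-year film is classified for non-union or avascular necrosis.

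**The concern.** The non-union definition needs a fracture that can still be seen one year after surgery. Arthroplasty takes away both the fracture and the native head. By the article's own background figures, most patients who develop non-union or fixation failure are re-operated, and arthroplasty is the operation implied.

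The event that makes the reading impossible is therefore the primary outcome, which PRP is meant to change. A comparison of 1-year films is conditioned on a post-randomisation event that depends on treatment. Neither safeguard in the text reaches this. A re-operated hip is not a protocol violation, and a search of records cannot produce a 1-year film of a fracture that no longer exists.

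Non-union is the most direct measure of the trial's rationale, that better healing reduces fixation failure. A null result caused by the definition could be read as evidence against that mechanism.

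**Working it through.** **Inputs from the article.** 100 participants per main arm (Sequence generation); about 20% mortality in year 1, two-sided 0.05 and a 15-point target difference (Power and sample size); 30% vs 15% as one Table 1 scenario; 90% of failures re-operated (Existing knowledge).

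**Assumptions.** Non-union equals fixation failure in frequency. A share r of failures is re-operated before the film and cannot be read. Deaths are unrelated to failure, leaving 100 × 0.8 = 80 per arm. The article gives no timing for the 90%, so r is varied.

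**Check of the formula against Table 1.** The article states no power for a secondary outcome. The usual pooled-variance formula gives, for 30% vs 15% at 80% power:

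n = [1.96√(2 × 0.225 × 0.775) + 0.842√(0.30 × 0.70 + 0.15 × 0.85)]² / 0.15² = 120.5, so 121.

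This matches the Table 1 entry, as a number per arm. The same formula gives about 62% power at 80 per arm.

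**Rate left to observe.** Among hips still readable, q = p(1 − r)/(1 − pr), from 80(1 − pr) hips.

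| r | Control: rate (hips) | PRP: rate (hips) | Difference (points) | Expected events | Power, chi-squared | Power, Fisher's exact |
|---|---|---|---|---|---|---|
| 0 | 30.0% (80) | 15.0% (80) | 15.0 | 24 vs 12 | 62% | 56% |
| 0.5 | 17.6% (68) | 8.1% (74) | 9.5 | 12 vs 6 | 40% | 34% |
| 0.8 | 7.9% (61) | 3.4% (70) | 4.5 | 4.8 vs 2.4 | 21% | 17% |
| 0.9 | 4.1% (58) | 1.7% (69) | 2.4 | 2.4 vs 1.2 | 13% | 8% |

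Chi-squared power is Φ[(difference − 1.96 SE₀)/SE₁], where SE₀ uses the pooled rate and SE₁ the separate rates. For r = 0.8: SE₀ = 0.0399, SE₁ = 0.0408, (0.0449 − 0.0782)/0.0408 = −0.815, giving 21%. Fisher power comes from summing binomial probabilities over all tables with p < 0.05, with hips rounded to whole numbers. From r = 0.5 upwards at least one expected count is below 10, so the plan's own rule points to the Fisher column.

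At 33% (the background figure) vs 18% with r = 0.9, the observed rates are 4.7% vs 2.1% and chi-squared power falls from about 59% to about 13%.

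**Direction.** The odds of q are p(1 − r)/(1 − p). With equal r in both arms, (1 − r) cancels: the odds ratio is (0.15/0.85)/(0.30/0.70) = 0.41 at every r. The relative risk moves slightly away from 1, from 0.50 to 0.43 (r = 0.8) or 0.42 (r = 0.9). With unequal shares, again at 30% vs 15%:

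- 90% control, 60% PRP: 0.03/0.73 = 4.1% vs 0.06/0.91 = 6.6%. The effect is reversed.
- 60% control, 90% PRP: 0.12/0.82 = 14.6% vs 0.015/0.865 = 1.7%. The effect is exaggerated.

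**Avascular necrosis.** The article gives no rate and no link with fixation failure. Take failure of 33% vs 18%, r = 0.9 and an assumed 10% risk in healed hips. If failed hips also carry 10%, dropping them changes nothing. If they carry an assumed 30%, 16.6% vs 13.6% becomes 10.9% vs 10.4%. The documents do not settle which applies.

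**The case against.** The strongest reply is that nothing in the article excludes re-operated hips. The analysis is declared intention-to-treat, earlier films and re-operations are recorded, and a full protocol or analysis plan that is not shown may count these hips as non-unions. A reader might infer that the planned tests deliberately drop the worst results; the text does not support that. What remains is that the endpoint definition itself is in the article and is tied to a single film. An analysis counting re-operated hips as non-union would have to depart from that wording.

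A reader might also infer that the comparison is biased toward no difference, hides a PRP effect, or must contradict the primary result. The working does not support this: equal shares leave the odds ratio unchanged, and unequal shares can push it either way. Nor can a hidden effect on avascular necrosis be claimed.

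Further points stand. The 90% figure has no timing. Arthroplasty is implied but not quantified, and a re-operation that keeps the native head may leave a readable hip. At r = 0.5 the loss is clearly smaller. Failure of fixation is also read at 6 and 12 weeks, so it is less exposed. The primary outcome counts these patients as events and is untouched.

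**Conclusion.** The concern holds in a limited form. The stated non-union definition cannot classify hips converted to arthroplasty before one year, and on the background figures these may be most of the true non-unions. Applied as written, the comparison loses events, absolute difference and power: 15 points shrink to about 2–5, and chi-squared power falls from about 62% to about 13–21% (8–17% with Fisher's exact test), if 80–90% of failures are re-operated and unreadable before the film. These sizes rest on that assumption and on 80 evaluable survivors per arm. The relative effect may be preserved, reversed or exaggerated, depending on the re-operated share in each arm. For avascular necrosis, hips converted early cannot be read, but the direction of any distortion is unknown. This deserves correction because non-union speaks directly to the healing rationale, but it does not threaten the primary analysis.

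**What to change.** - **Non-union:** define the event as non-union on the 1-year film, or re-operation for failure of fixation or non-union before that film.
- **Failure of fixation:** report it cumulatively by 6, 12 and 52 weeks, with such re-operations counted as events.
- **Avascular necrosis:** count re-operation for avascular necrosis as an event, and show hips converted before one year for other reasons separately by arm, with no claim about direction of bias.
- **Denominators:** give the number evaluable per arm for each outcome. Show deaths without a prior event separately; a plain all-randomised denominator would silently count them as non-events.

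The cost is wording. Re-operation is already collected at each visit, and the primary outcome already needs its reason; re-operation for avascular necrosis must be identifiable in the same way. The drawback is that the revised non-union outcome will overlap heavily with the primary outcome, so it should not be presented as independent confirmation. The film-only result can be kept as a description of the hips still readable.

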#### Measures of harm and adverse events

##### Expected Adverse Events

• Wound infection

• Venous thrombo-embolic phenomena

• Death

• Pneumonia

• Urinary tract infection

• Blood transfusion

• Failure of fixation

• Cerebrovascular accident

• Acute coronary syndrome

• Myocardial infarction

• Deep vein thrombosis

#### Power and sample size

The minimum clinically important treatment effect of PRP was agreed in discussion with several expert orthopaedic trauma surgeons. Although the figures varied by surgeon, all agreed that an absolute reduction of 15% in fixation failure would be clinically important. The overall rate of fixation failure of all intracapsular fractures of the femur is reported to be 20-35% [10]. Table 1 shows the total sample size with two-sided significance set at 0.05 for various scenarios of minimum clinically relevant difference. Sample sizes were determined using the PS power and sample size software [11].

**Table 1 T1:** Sample sizes calculated for various scenarios

Rate of failure in control group (%)	Rate of failure in the intervention group (%)					
	
	10		15		25	
	
	80% power	90% power	80% power	90% power	80% power	90% power
25	100	133				

30	62	82	121	161		

35	43	57	73	97	329	440

The mortality of patients with intracapsular fractures of the proximal femur is approximately 20% during the first year and this needs to be taken into account in the sample calculation. A recruitment target of 200 participants provides a good margin for unanticipated recruitment problems and loss to follow-up.

In the absence of an agreed method to determine the sample size for a pilot study a group of expert orthopaedic surgeons were consulted. All agreed that a sample of 25 participants in the fixed-angle screw and plate group would be sufficient to provide adequate pilot data.

From a recent audit carried out in our department we know that approximately 450 fractures of the proximal femur are treated operatively per year at University Hospital Coventry and Warwickshire. Approximately 250 of these patients would be eligible for inclusion into this trial. Therefore, even accounting for significant loss to follow-up, the trial sample can be recruited in one year.

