#### Treatment allocation

##### Sequence generation

The allocation sequence will be generated randomly. The randomisation will be weighted such that at the end of the trial there will be 25 participants in the fixed-angle screw and plate group and 100 participants in each of the remaining groups. Randomisation will be stratified by displacement of the fracture. Fractures will be defined as undisplaced (Garden grade I or II) or displaced (Garden grade III or IV); Garden's classification of intracapsular fractures is well recognised and universal and it has been validated to distinguish between grades I and II compared with III and IV [12,13]. The surgery will be performed by any of the 16 Consultant Surgeons, two Associate Specialists and 14 Trainees at the University Hospital Coventry and Warwickshire. The large number of surgeons and the wide skill mix should eliminate the 'surgeon effect' such that stratification by surgeon is not required.

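### Table 1 is labelled as total sample size but gives numbers per group, so 200 leaves no margin for a 15-point reduction when control failure is 25-35%

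*Protocol article*

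**What the plan says.** Under Power and sample size, the article sets the target effect: "all agreed that an absolute reduction of 15% in fixation failure would be clinically important". For the control rate it says "The overall rate of fixation failure of all intracapsular fractures of the femur is reported to be 20-35" per cent. It then introduces the table: "Table 1 shows the total sample size with two-sided significance set at 0.05 for various scenarios of minimum clinically relevant difference". The table is titled "Sample sizes calculated for various scenarios" and covers six pairs of failure rates at 80% and 90% power. Two of those pairs are 15 points apart: 25% versus 10% (100 and 133) and 30% versus 15% (121 and 161).

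The same section adds: "The mortality of patients with intracapsular fractures of the proximal femur is approximately 20% during the first year", and says the calculation has to allow for this. It concludes: "A recruitment target of 200 participants provides a good margin for unanticipated recruitment problems and loss to follow-up".

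Sequence generation fixes the allocation as "25 participants in the fixed-angle screw and plate group and 100 participants in each of the remaining groups". The 200 is therefore the combined size of the PRP and control groups. Nowhere does the article describe the Table 1 figures as per group.

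**The concern.** The label decides whether 200 is generous or bare. Read as totals, 100 and 121 sit well below 200, and the margin sentence makes sense. Read as numbers per group, they mean 200 and 242 in total, and 200 has nothing to spare for either 15-point scenario.

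PRP versus control is the only hypothesis-testing comparison in the trial (Design summary), and it is judged at p<0.05 (Analysis of efficacy). A reader weighing its result needs to know the power it had for the difference the surgeons agreed was important. As written, the article tells that reader there was power to spare.

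**Working it through.** **Inputs.** Two-sided alpha 0.05, 80% and 90% power, the failure rates in Table 1, the 15-point target, the 20-35% control range and 20% one-year mortality all come from Power and sample size. The 100 per compared group comes from Sequence generation. The test comes from Analysis of efficacy: chi-squared, replaced by Fisher's exact test when a cell is below 10.

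**Step 1: reproduce Table 1.** The uncorrected chi-squared formula with equal groups is

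n per group = [1.96·√(2·p̄·q̄) + z_β·√(p₁q₁ + p₂q₂)]² / (p₁ − p₂)², where p̄ is the mean of p₁ and p₂.

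For 25% versus 10% at 80% power, p̄ = 0.175:

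[1.96·√0.28875 + 0.8416·√0.2775]² / 0.15² = 99.5, rounded up to 100.

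| Control v PRP (%) | n per group, 80% / 90% | Printed | Correct two-arm total |
|---|---|---|---|
| 25 v 10 | 99.54 / 132.76 | 100 / 133 | 200 / 266 |
| 30 v 10 | 61.60 / 81.96 | 62 / 82 | 124 / 164 |
| 35 v 10 | 42.60 / 56.52 | 43 / 57 | 86 / 114 |
| 30 v 15 | 120.47 / 160.78 | 121 / 161 | 242 / 322 |
| 35 v 15 | 72.39 / 96.41 | 73 / 97 | 146 / 194 |
| 35 v 25 | 328.47 / 439.23 | 329 / 440 | 658 / 880 |

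All 12 entries match as numbers per group and none matches as a total. Two variants do not rescue the label: for 25 v 10 at 80% power, a continuity correction gives a total of 226 and a one-sided alpha gives 158. If the printed numbers were totals, the 80% columns would deliver about 50% power and the 90% columns about 63%.

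**Step 2: test the margin.** To allow for 20% loss, divide by 0.8.

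- Entries taken as totals, at 80% power: 100/0.8 = 125 and 121/0.8 = 151.25. Both are well under 200.
- Entries taken per group, as they are: 100/0.8 = 125 per group, or 250 in total; 121/0.8 = 151.25, so 152 per group, or 304 in total. Both exceed 200.

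**Step 3: power that 100 per group delivers.** The formula column inverts the expression above. The planned-rule column enumerates all pairs of binomial outcomes, using Fisher's test when any cell is below 10 and chi-squared otherwise. The 80 per group is 100 × (1 − 0.20).

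| Control v PRP (%) | 100 per group: formula / planned rule | 80 per group: formula / planned rule |
|---|---|---|
| 20 v 5 | 90% / 88% | 82% / 79% |
| 25 v 10 | 80% / 81% | 71% / 67% |
| 30 v 15 | 72% / 73% | 62% / 63% |
| 35 v 20 | 66% / 67% | 57% / 58% |

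The rule matters most where PRP failures are few. At 80 per group it invokes Fisher's test in about 72% of outcomes for 25 v 10 and 99% for 20 v 5.

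**Step 4: larger effects.** At 80 per group the formula gives 84% for 35 v 15, 89% for 30 v 10 and 97% for 35 v 10.

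**The case against.** The label error is not open to dispute, but several stronger readings are.

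- **Power is simply 57-71%.** A reader might infer this from the 20% mortality. It requires every death to leave the primary analysis, and the article does not say so. The outcome is a proportion re-operated within one year, analysed by intention to treat. It was chosen to limit missing data, with several sources for it. A participant who dies without re-operation could be counted as a known non-event. With all 100 per group analysed at the assumed rates, power for control rates of 25-35% is 66-80%. This objection stands, so both cases must be given.
- **There is no margin in any scenario.** This is not so. Reductions of 20-25 points keep 84-97% power after 20% loss, and 20 v 5, at the bottom of the cited control range, keeps about 79-82%.
- **Only a 20% control rate keeps power above 80% for a 15-point reduction after losses.** That holds by the chi-squared formula (82%) but not under the article's own Fisher rule (79%).
- **The target of 200 was derived from misreading the table.** This cannot be shown. One hundred per arm is also the correct per-group figure for 25 v 10 at 80% power, so the label could be a slip of wording. The margin sentence would still be wrong for the 15-point effect.
- **Leaving out 35 v 20 is an error, or a null result could never exclude a 15-point benefit.** Neither follows. The table offers only a selection of scenarios, and what a null result excludes depends on the confidence interval observed.

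**Conclusion.** The point holds within stated limits. Table 1 gives numbers per group, and calling them totals understates every requirement by half. With 100 per group, 200 exactly meets 25 v 10 at 80% power without losses. It falls 42 short for 30 v 15 (242 − 200) and reaches 90% power for neither (266 and 322 needed). The margin claim is therefore unsupported for the agreed 15-point reduction at control rates of 25-35%. This is so whether or not deaths are removed from the analysis; their handling only decides how large the shortfall is. The conclusion rests on equal groups, two-sided 0.05 and the article's own failure rates. It does not extend to a 20% control rate or to reductions of 20-25 points.

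**What to change.** 1. In the sentence introducing Table 1, describe the figures as the sample size per group.
2. Replace the margin sentence with the power of 100 per group for a 15-point reduction:
   - if all participants are analysed: about 80% (25 v 10), 72-73% (30 v 15) and 66-67% (35 v 20);
   - if the stated 20% mortality removes participants from the primary analysis: about 67%, 63% and 58% under the planned chi-squared/Fisher rule (71%, 62% and 57% by the chi-squared formula), and about 79-82% for 20 v 5.
3. State which of the two assumptions about deaths applies to the primary analysis.

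Adding a 35 v 20 cell to the table (138 per group at 80% power) is optional. No extra patients are required. The only cost is a less favourable stated power.
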